## Introduction

1

Amyotrophic lateral sclerosis (ALS) is a progressive and fatal neurodegenerative disorder of the human motor system, with median survival of 3 to 5 years.^[1,2]^ The currently licensed treatments for ALS include riluzole [anti-glutamatergic agent]^[3–5]^ and edaravone,^[6]^ both of which provide limited benefits. The etiology of sporadic ALS remains unresolved, although a complex multistep interaction between genetic and molecular processes, along with environmental influences, seems likely.^[2,7,8]^ Over the past several decades there have been more than 250 separate clinical studies searching for an effective treatment for ALS, none of which were successful in slowing the progression of ALS.^[9,10]^

There is accumulating evidence for a role of neuroinflammation in ALS pathogenesis, with astrocytes, microglia and T cells actively contributing to neurodegeneration and disease progression in ALS.^[11–16]^ Specifically, reduced expression of mutant superoxide dismutase one (SOD1) protein in microglia^[17]^ and astrocytes^[18]^ has been associated with a slower rate of disease progression. In addition, elimination of functional CD4^+^ T cells accelerates the rate of disease progression in SOD1 mouse models, a process that can be rectified by reconstitution of the immune system through bone marrow transplantation.^[12,19]^

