### Aims and objectives

2.1

The primary aim of this clinical trial as to assess the efficacy of tecfidera (dimethyl fumarate, DMF) on disease progression in sporadic ALS patients. The secondary aim of this study is to assess effects of tecfidera in sporadic ALS patients on survival, lower motor neuron dysfunction, respiratory dysfunction, quality of life as well as safety and tolerability. The primary and secondary aims of this will be achieved through a multi-center, randomized, double-blind, placebo controlled clinical trial conducted on sporadic ALS patients that will be prospectively recruited from 6 ALS centers in Australia. The total study duration will be 40 weeks, with a 36-week study period and an end of study visit occurring at 40 weeks or at early termination/withdrawal from study.

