### Secondary outcome measures

2.3

The secondary outcome measures will be measured at screening, baseline, week 12, 24, 36 and 40. The secondary endpoints will include measures of efficacy and safety.

1.SurvivalSurvival will be defined from symptom onset to death of patients or tracheostomy insertion, whichever occurs first and will be measured in months.2.Lower motor neuron functionLower motor neuron function will be assessed by clinical and neurophysiological biomarkers and will included muscle strength and motor amplitudes.**-Muscle strength**(a) *Medical Research Council score*: Clinical assessment of muscle strength will be made by the Medical Research Council (MRC) score. The MRC score is a standard clinical score used in clinical practice and will be performed by the neurologist at each site. This score assesses muscle strength on a 5-point score as follows:5 = Normal strength.4 = Active movement against gravity and resistance.3 = Weak contraction against gravity.2 = Active movement with gravity eliminated.1 = Minimal contraction.0 = Complete paralysis.The following movements will be assessed in each patient:*-Upper limbs*: Shoulder abduction, elbow flexion, elbow extension, wrist extension, finger extension, finger abduction, and thumb abduction on both sides. The total score when strength normal in the upper limbs will be 70.*-Lower limbs*: Hip flexion, abduction, adduction and extension, knee flexion and extension, and ankle dorsiflexion and plantarflexion. The total score when strength is normal in the lower limbs will be 80. The upper and lower limb MRC scores will be combined yielding a maximum score of 150 (0 severe weakness to 150 normal strength).(b) *Hand dynamometry*: Muscle strength will also be assessed by hand-held dynamometry (JAMAR PLUS, Patterson Medical, Warrenville, IL). A spring-loaded device that “breaks” at pre-set forces will be used to assess readings obtained by hand-held dynamometry throughout the study. Wherever possible, the same rater will be used at each site for each assessment. Grip strength dynamometry for both hands will be acquired, and the mean force in kilograms will be calculated. Measures will be obtained from each hand in triplicate-*Neurophysiological testing:* The degree of lower motor neuron loss will be determined neurophysiological testing performed on nerve conduction study machines (Nicolet EDX, System, Natus, Middleton, WI). The following parameters will be recorded from the intrinsic hand muscles on both sides.(a) *Neurophysiological Index (NPI)*: This is an established measure of lower motor neuron dysfunction in ALS.^[36]^ The NPI will be calculated from by stimulating the median nerve at the wrist and recording the motor response from the abductor pollicis brevis muscle using the following formula: 

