### Baseline (Visit 2) Week 0 (14 days post visit 1)

3.2

All patients will have their inclusion and exclusion criteria checked at the Baseline Visit (Week 0) and eligible patients will be randomized to either active group (Tecfidera) or control group (placebo) in a 2:1 ratio and the IP will be dispensed. Randomization will be performed by a third party (Cenduit) working with the CRO, using an Interactive Web Response System with random number generation. The numbers will be emailed to a designated pharmacist at each sit and bottles will be labeled by the randomly generated number. All parties at each site will be blinded, and unblinding will only occur after data analysis. This study visit will also involve an assessment of ALSFRS-R, vital signs (blood pressure, pulse rate, temperature, and respiratory rate), and any changes to concomitant medications. Urine samples will be collected for safety monitoring (urinalysis). In addition, women of childbearing potential will undergo another urine pregnancy test.

### Treatment Period (Visits 3, 4, and 5) Weeks 12, 24, and 36

3.3

Patients will return to the site at Weeks 12, 24, and 36 for neurological and physical examinations. Their weight, BMI, and vital signs (blood pressure, pulse, temperature, and respiratory rate) will be recorded. The visit will also involve an assessment of ALSFRS-R, NPI and SI, FVC as measured by handheld spirometer, SNIP test, quantitative hand muscle testing by dynamometry, and global strength as measured by the MRC score. All patients will undergo laboratory evaluation of hematological and biochemical parameters as well as urinalysis. In addition, women of childbearing potential will undergo a urine pregnancy test and urine will also be collected to test neurotrophin receptor P75 levels (secondary endpoint). If the patient consented for additional research in future, blood samples (additional) will be collected for storage. At Week 12 and 36, an ALSSQOL-R questionnaire will be completed by patients and the IP will be dispensed at Week 12 and Week 24.

### End of Study (Visit 6) Week 40

3.4

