### Statistical methods

3.6

The statistical analysis will be performed using statistical analysis system (SAS) Version 9.4. All details regarding the statistical analysis and the preparation of tables, listings, and figures will be described in the Statistical Analysis Plan (SAP) and approved by the Sponsor before database lock. The default summary statistics for continuous variables include number of contributing observations (n), mean, SD, median, minimum, and maximum. For categorical variables, the number and percentage (in each category will be the default summary presentation. “Baseline” is defined as the last observed value of the parameter of interest prior to the first intake of IP (this includes unscheduled visits). For numerical variables, change from Baseline will be calculated as the difference between the value of interest and the corresponding Baseline value. All formal statistical tests will be two-sided at the 5% significance level. Point estimates of treatment differences will be accompanied with a two-sided 95% confidence intervals. In the case of normality assumption violations, appropriate non-parametric methods will be used for analysis. All data will be presented in by-patient listings.

The following analysis populations will be defined as follows:

i.*Intent-to-Treat (ITT) Population*- The ITT population will include all randomized patients. In this population, treatment will be assigned based upon the treatment arm to which patients were randomized regardless of which treatment they received;ii.*Safety Population (SAF)*- The SAF includes patients who are randomized and took at least 1 dose of the IP. The safety analysis will be conducted according to the treatment that a patient actually receives;iii.*Per Protocol Population (PP)-* The PP population will include all patients who do not have major protocol deviations that would affect the evaluation of the primary efficacy endpoint.

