The primary endpoint (ALSFRS-R change at 36 weeks) will be analyzed using Mixed Model for Repeated Measures with treatment as fixed effect and Baseline ALSFRFS-R score as covariate. For the active treatment versus placebo comparison, the results will be presented in terms of an estimated treatment difference together with its associated 95% confidence intervals and 2-sided *P* value. Possible effects of other covariates will also be investigated. Missing data handling and possible sensitivity analysis will be described in the SAP. Details of specific alternative statistical methods in the event model assumptions are violated will be documented in the SAP.

Efficacy analysis for secondary endpoints (see outcome measures section) will be summarized and evaluated using the ITT population. Safety analyses will be performed using SAF. All safety data will be provided in by-patient listings. The safety variables that will be analyzed are outlined in Table 1. No interim analysis is planned for the study. All statistical analysis has been performed by the IQUVIA (CRO) biostatisticians in consultation with the PIs ([name] and [name]).

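### Survival is timed from symptom onset although patients are at risk in the trial only from randomisation; without delayed entry the reported survival estimates will be inflated

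*Protocol article*

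**What the plan says.** Section 2.1 of the protocol article makes survival an efficacy question about treatment: "The secondary aim of this study is to assess effects of tecfidera in sporadic ALS patients on survival". Section 2.3 fixes the clock and the event: survival "will be defined from symptom onset to death of patients or tracheostomy insertion, whichever occurs first and will be measured in months".

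The observation window is much shorter than that clock. In section 3.2, at Week 0, "eligible patients will be randomized to either active group (Tecfidera) or control group (placebo) in a 2:1 ratio". Section 2.1 adds: "The total study duration will be 40 weeks, with a 36-week study period and an end of study visit occurring at 40 weeks".

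On analysis, section 3.6 says only this about the secondary endpoints: "Efficacy analysis for secondary endpoints (see outcome measures section) will be summarized and evaluated using the ITT population". It also sets a general rule: "All formal statistical tests will be two-sided at the 5% significance level". It names means and medians as default summaries for continuous variables and leaves further detail to an SAP that is not shown. Nothing in the article restarts the survival clock at randomisation or provides for entry into the risk set at that date.

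**The concern.** A patient who died between onset and the point of entry could not have been randomised. For those who were randomised, the interval from onset to Week 0 is therefore free of deaths by selection (immortal time), and treatment cannot act on it. A Kaplan-Meier curve that starts every patient at onset counts them as at risk during months when their death could not have been observed. Its denominators are too large, and the curve and median come out too high.

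Onset-to-entry time also varies between patients. A raw comparison of months survived would consist largely of pre-treatment time, and its spread would add noise to a comparison of only 60 and 30 patients. The survival result could then be misread, although the secondary aim is the effect of tecfidera after treatment starts.

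**Working it through.** The article gives no event count, hazard ratio or power for survival, so there is no stated figure to reproduce. The check asks how much the time origin matters.

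**Inputs from the article:** maximum follow-up 40 weeks; 60:30 allocation (section 2.4); two-sided 5% level; median survival of 3 to 5 years, that is 36 to 60 months (Introduction).

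**Assumptions, not in the article:** mean onset-to-randomisation delay 12 to 24 months, SD 8 to 16 months, exponential survival. Eligibility is in Table 2, which is not reproduced, so any limit on disease duration is unknown.

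**1. Share of counted time before entry.** Follow-up = 40/4.345 = 9.2 months. With complete follow-up:
- mean delay 12 months: 12/(12 + 9.2) = 57%
- mean delay 24 months: 24/(24 + 9.2) = 72%

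In simulation, where deaths shorten follow-up, the share is about 58% to 73%.

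**2. Survival curve.** With a true median of 36 months, S(24) = 0.5^(24/36) = 63% and S(36) = 50%. Delay is gamma with mean 18 and SD 12 months, and only patients still alive at that point are randomised. The onset-based Kaplan-Meier without delayed entry then gives about 86% at 24 months and 75% at 36 months. With entry into the risk set at randomisation it returns about 63% and 50%.

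A second set of simulations used a less dispersed delay (SD half the mean, limited to 1 to 36 months), specified among those randomised:

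| True median 36 months; mean delay | True S(24) | Onset clock, no delayed entry |
|---|---|---|
| 12 months | 0.63 | 0.81 |
| 18 months | 0.63 | 0.88 |
| 24 months | 0.63 | 0.93 |

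Across true medians of 36 to 60 months the range is 0.81 to 0.95 against a true 0.63 to 0.76.

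**3. Event rate.** The true rate is ln 2/36 = 0.0193 per month. On the plain onset clock it is 0.0081, 0.0062 and 0.0053 for mean delays of 12, 18 and 24 months. The understatement runs from 0.0193/0.0081 = 2.4-fold to 0.0193/0.0053 = 3.6-fold. Counting only time after randomisation gives 0.019 to 0.020.

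**4. Comparison between arms.** Log-rank simulations used 60:30 patients and 1000 runs per scenario.
- *No treatment effect:* rejection on the onset clock ranged from 0.036 to 0.062. The Monte Carlo standard error is sqrt(0.05 × 0.95/1000) = 0.007, so this is compatible with 0.05.
- *Hazard ratio 0.4, true median 24 months:* power from onset against from randomisation was 0.37 v 0.39 (mean delay 12 months) and 0.39 v 0.42 (24 months).
- *Hazard ratio 0.4, true median 36 or 48 months:* no loss was visible, for example 0.31 v 0.31 and 0.25 v 0.24.
- *A separate Cox simulation* (800 runs, 25% placebo events, hazard ratio 0.4) gave 42.0% from onset against 46.9% from randomisation. A 25% event rate implies a median of 9.2 × ln 2/(−ln 0.75) = 22 months, below the article's range.

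**5. Raw months.** The standard error of the difference in mean delay is SD × sqrt(1/60 + 1/30) = SD × 0.2236. The 95% chance range is ±1.96 × 8 × 0.2236 = ±3.5 months for SD 8 and ±1.96 × 16 × 0.2236 = ±7.0 months for SD 16. This sits beside 9.2 months of follow-up and applies to a simple difference in months survived from onset, not to a hazard ratio or log-rank test.

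**The case against.** The strongest reply is that section 2.3 fixes a time scale and an event but no estimator, risk set or censoring rule, and that section 3.6 leaves analytic detail to the SAP. Onset can be a valid time scale if each patient enters the risk set at randomisation, and the SAP may say so. The article also promises no survival curve or median from onset; its stated interest is the effect of treatment.

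Part of this stands. The inflation is conditional on an analysis without delayed entry, and a reader who inferred that timing from onset must give a wrong survival estimate would go beyond the document. But the time origin is not a detail left open: the protocol states it, and nothing shown supplies the step that would make it valid. The SAP would have to add that step or override the definition.

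A reader might also infer that chance imbalance in disease duration would pass for a treatment effect, or that the test is biased. The document does not support that. Pre-entry time is balanced in expectation by randomisation, and the test's size already allows for chance imbalance. The ±3.5 to ±7.0 months matter only if raw months are compared.

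It is also fair to say that the delays are assumed. They set the size of the inflation, not its direction.

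**Conclusion.** The point holds in conditional form. As defined, and without delayed entry, the survival endpoint counts death-free months before entry and overstates absolute survival. With an assumed mean delay of 18 months and a true median of 36 months, the error is about 23 percentage points at 24 months (86% v 63%) and 25 at 36 months (75% v 50%). These figures rest on exponential survival and assumed delays.

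The comparison between arms is hardly affected: size is kept, the power loss is zero to about 5 points in the scenarios above, and neither arm is favoured. Survival is one of several secondary endpoints, and the primary ALSFRS-R analysis and the sample size are untouched. The definition should be corrected, but it does not invalidate the trial.

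**What to change.** In section 2.3 and the SAP, define survival as time from randomisation to death or tracheostomy, whichever comes first. Censor at Week 40 or at the last date known alive without tracheostomy. Include onset-to-randomisation time as a baseline covariate in the Cox model. If survival from onset is also reported, state that patients enter the risk set at randomisation (left truncation), and do not compare raw months from onset between arms.

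The cost is one changed definition and a sentence on delayed entry. The present definition already needs the onset and event dates, and the randomisation date is known, so no new data are required. Section 3.6 has the SAP approved before database lock, which leaves a point at which the change can be made.

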
**Table 1 T1:**
[figure not shown]
Adverse reactions reported with tecfidera.

Serious adverse events are defined as any event that results in death, disability or incapacity, is life threatening, or leads to congenital abnormality/birth defect. Hospitalization for any medical event, other than elective surgery, will also be deemed an SAE. All opportunistic infections and malignancies will be considered as SAEs. The investigator will make an assessment of the seriousness and causality of each AE and SAE.

### Patient enrolment and withdrawal

2.4

*Sample size calculation*: Based on previous clinical studies and literature,^[44,45]^ it was assumed that the mean difference in the ASLFRS-R score between active and placebo group at 36 weeks will be 7 [common standard deviation of 8%]. A clinically important response rate on Tecfidera was defined as 0.9, and with a 2:1 (Tecfidera:Placebo) allocation, 90% power, 5% statistical significance rate and 20% dropout rate, we estimated that 90 patients (60:30) need to be randomized inorder to attain the primary outcome measure. The inclusion and exclusion criteria are outlined in Table 2.

**Table 2 T2:**
[figure not shown]
The inclusion and exclusion criteria for TEALS study.

## Study design

3

Investigator led Phase II multi-center, randomized, placebo controlled, double blind clinical trial assessing the efficacy and safety of Tecfidera in patients with sporadic ALS. Study procedures will be performed as detailed in the Schedule of Events Flow Chart in Table 3.

**Table 3 T3:**
[figure not shown]
Schedule of events for the TEALS study.

### Screening Visit (Visit 1) -14 days

3.1

Patients will be screened for the study after signing an approved Informed Consent Form (ICF). As part of the screening, patient's extensive medical and neurological history will be recorded. Inclusion/exclusion criteria will be evaluated and the vital signs (blood pressure, pulse, temperature, and respiratory rate) will be recorded. Physical and neurological examinations will be performed. Patient's height and weight will be measured and body mass index (BMI) will be calculated. The visit will also involve an initial assessment of ALSFRS-R, NPI and SI, FVC as measured by handheld spirometer, SNIP test, quantitative hand muscle testing by dynamometry, and global strength using MRC score. Prior/ongoing medications will be recorded. All patients will undergo laboratory evaluation of hematological and biochemical parameters; hepatitis B, C, and human immunodeficiency virus (HIV) serology; and urinalysis. In addition, women of childbearing potential will undergo a urine pregnancy test. Urine will also be collected for neurotrophin receptor P75 levels (secondary outcome). An ALSSQOL-R questionnaire will be completed by the patient at screening.

### Baseline (Visit 2) Week 0 (14 days post visit 1)

3.2

All patients will have their inclusion and exclusion criteria checked at the Baseline Visit (Week 0) and eligible patients will be randomized to either active group (Tecfidera) or control group (placebo) in a 2:1 ratio and the IP will be dispensed. Randomization will be performed by a third party (Cenduit) working with the CRO, using an Interactive Web Response System with random number generation. The numbers will be emailed to a designated pharmacist at each sit and bottles will be labeled by the randomly generated number. All parties at each site will be blinded, and unblinding will only occur after data analysis. This study visit will also involve an assessment of ALSFRS-R, vital signs (blood pressure, pulse rate, temperature, and respiratory rate), and any changes to concomitant medications. Urine samples will be collected for safety monitoring (urinalysis). In addition, women of childbearing potential will undergo another urine pregnancy test.

### Treatment Period (Visits 3, 4, and 5) Weeks 12, 24, and 36

3.3

Patients will return to the site at Weeks 12, 24, and 36 for neurological and physical examinations. Their weight, BMI, and vital signs (blood pressure, pulse, temperature, and respiratory rate) will be recorded. The visit will also involve an assessment of ALSFRS-R, NPI and SI, FVC as measured by handheld spirometer, SNIP test, quantitative hand muscle testing by dynamometry, and global strength as measured by the MRC score. All patients will undergo laboratory evaluation of hematological and biochemical parameters as well as urinalysis. In addition, women of childbearing potential will undergo a urine pregnancy test and urine will also be collected to test neurotrophin receptor P75 levels (secondary endpoint). If the patient consented for additional research in future, blood samples (additional) will be collected for storage. At Week 12 and 36, an ALSSQOL-R questionnaire will be completed by patients and the IP will be dispensed at Week 12 and Week 24.

### End of Study (Visit 6) Week 40

3.4

After completing Week 36 procedures, all patients will return to the study site at Week 40 for the End of Study Visit (4 weeks after the end of treatment visit). Patients who discontinue the study early will be asked to return to the study site for the early termination procedures 4 weeks after their last dose of Tecfidera/placebo. At this visit, neurological and physical examination will be performed and vital signs (blood pressure, pulse, temperature, and respiratory rate) will be recorded. The visit will also involve an assessment of ALSFRS-R, NPI and SI, FVC as measured by handheld spirometer, SNIP test, quantitative hand muscle testing by dynamometry, and global strength using MRC score. All patients will undergo laboratory evaluation of hematological and biochemical parameters as well as urinalysis. Urine will also be collected to test neurotrophin receptor P75 levels (secondary endpoint). An ALSSQOL-R questionnaire will also be completed by all patients. Adverse events and changes to concomitant medications will be observed and evaluated.

